## Abstract

**Background:**

Compassionate support at the end of life should not be the responsibility of health and social care professionals alone and requires a response from the wider community. Volunteers, as community members, are a critical part of many end-of-life care services. The impact of their services on important outcomes such as quality of life is currently poorly understood. The purpose of this study is to evaluate a series of social action initiatives which use volunteers to deliver befriending services to people anticipated to be in their last year of life. The aim is to determine if receiving care from a social action volunteer befriending service plus usual care significantly improves quality of life in the last year of life.

**Methods/design:**

The research questions will be addressed through a wait-list randomised controlled trial (WLRCT) and qualitative case study evaluation across 12 sites in England. Participants will be randomly allocated to either receive the social action volunteer befriending service straight away or receive the intervention after a four week wait (wait-list arm). The impact of the intervention on end-of-life experience (quality of life as primary outcome, loneliness, social support) will be measured. Repeated assessments will be carried out at baseline and weeks 4 and 8 for the intervention arm and weeks 4, 8 and 12 for the wait-list arm. For selected sites case study evaluation will include interviews, observation and documentary analysis to understand the mechanisms underpinning any found impact.

**Discussion:**

This study will address the need to both provide services which use social action models to support end-of-life care in community settings, and to robustly evaluate these models to determine if they influence the experience of end-of-life care. Such services could work to reduce isolation, help meet emotional needs and maintain a sense of connectedness to the community. ISRCTN 12929812 Registered 20.5.15

## Background

Providing excellent end-of-life care (defined here as care in the last year of life) that is responsive to need is critically important. People want to be cared for as close to home as possible, especially in the last year of life [1]. However there is poor understanding about which components of home based interventions provide the highest benefit [2, 3]. Understanding the impact of these components in context is important so that priority is given to developing services in a way known to maximise benefit to people in their last year of life, informal carers and the services themselves.

With reference to end of life care at home, it is increasingly recognised that compassionate support cannot be the responsibility of health and social care professionals alone and requires a response from the wider community. Volunteers are a critical part of many end-of-life care services [4–11] Family members are satisfied with the services that volunteers provide at the end-of-life [9], but there is little evidence of their effect on care outcomes. A recent systematic review assessing the impact of volunteers involved in the direct care of palliative care patients and their families at the end-of-life only found 8 studies, none from the UK. They indicate that volunteer involvement has a positive impact on satisfaction with care and that people may survive longer with home visits from a volunteer. They conclude that further research is needed to ensure the resource of volunteers in palliative care is used appropriately and effectively. Evaluation in well-designed comparative studies is recommended [12].

In order to meet this knowledge gap, the UK Cabinet Office funded the provision and evaluation of a range of social action projects at the end of life. The purpose of this evaluation is to use a robust and ethical comparative design to determine the effect of volunteer led social action befriending services on quality of life in the last year of life and how such services can best be implemented and delivered. Research of this sort can ensure that the resource of volunteers in palliative care is used appropriately, and in a way which effectively improves quality of life and the experience in the last year of life. Many volunteer delivered befriending social action services are being run or developed to provide non-clinical support to people in their own homes such as companionship, running errands and providing information. Whilst this feels intuitively helpful, there is no robust evaluation of the outcomes of these services nor understanding of how best to provide such care to maximise effectiveness.

## Methods/design

### Aims

The **primary aim** of the study is to evaluate the effectiveness of receiving care from a social action volunteer befriending service plus standard care at improving quality of life as compared to usual care alone for adults in the last year of life.

The **secondary aims** are to:explore whether the social action volunteer befriending service reduces loneliness and affects the perception of social support for adultsexamine whether informal carers for those receiving care from a social action volunteer befriending service experience less carer burdendetermine whether receiving care from a social action volunteer befriending service can affect participant’s use of other health and social care servicesidentify and explore the factors that influence the impact of social action volunteer befriending services on end-of-life experience

### The intervention

The intervention is based on a model of social action, and comprises a number of components. Core to the intervention is that it is provided by a trained volunteer rather than a paid member of staff, and provides non-clinical, non-hands on support. Individual support needs are assessed by the non-clinical volunteer co-ordinator, and support then provided from a suite of possible options including ‘befriending’ e.g. sitting with someone to provide companionship, ‘practical support’ e.g. assisting with household tasks such as dog walking, gardening, picking up prescriptions or other errands, and ‘signposting’ e.g. providing information on other available services. Support will be typically provided from 1–3 times per week, face to face or by telephone, as negotiated between volunteer providers and participants. Participants will be in the trial for 8 or 12 weeks (immediate vs wait-list arm), but their receipt of the social action volunteer service can continue outside the trial beyond this point if needed. Participants are free to withdraw at any time. Participants will continue to receive all usual care during this period. In this study the intervention will be provided across a number of sites in England who are independently funded to provide this service by the UK Cabinet Office.

### Methods

The study involves two main approaches to data collection.

#### Wait-list randomised controlled trial

This is a multi-site (*n* = 12) randomised controlled trial (RCT) involving a wait-list design. Participants will be allocated on a 1:1 allocation ratio. A wait-list trial was chosen as an ethical design which has the strength of an RCT, but with greater acceptability as all patients eventually receive the intervention. In a wait-list trial, respondents are either allocated to an intervention group where they receive the intervention immediately (or as soon after randomisation as possible) or to a wait-list group where they receive the same intervention after a defined period on a waiting list. While they are on the waiting list patients receive standard/usual care. Wait-list designs have been successfully used in end-of-life care research, including where there is a pre-existing service [13, 14]. Advantages include having the strength of a RCT in determining causality, but with greater acceptability as all patients eventually receive the intervention which can feel more ethically defensible in end of life care [13–18]. We propose a short wait period to minimise risk and acknowledge that interventions need to be effective in a short time period where life expectancy is short (i.e. a year or less) and attrition due to illness or death highly anticipated [19].

#### Qualitative case study design

Results generated from the WLRCT will be combined with a qualitative case study evaluation to understand the impact of social action befriending services on end-of-life experience and the factors that can maximize or minimise that impact. Each site providing the service comprises a case. The qualitative work stream (case study evaluation) comprises three distinct research activities within each chosen case study site:qualitative interviews with i) Patient participants and informal carers both receiving and having waited to receive the intervention to explore their experience of the service (*n* = 3-6); ii) volunteer staff providing the intervention to explore their experience of providing care, motivations, training, and the research study design etc. (*n* = 3-6); and iii) staff e.g. social action volunteers key manager/coordinator, other responsible stakeholders e.g. chief executive or general manager, clinical care staff etc. to explore organizational culture, history of the programme, selection, training and support of volunteer/ social action team. Interviews will last approximately an hour and will be conducted either face to face or via phone/skype. All participants taking part in the interviews must be able and willing to give informed consent.Non participant observation of relevant organizational meetings, workload allocation, decision-making activities etc.Documentary data such as service policies, job descriptions and other relevant written materials about the services provided as well as contextual data from the end-of-life care intelligence network on issues such as place of death etc.

## Study setting

Twelve individual sites across England will participate in this study. Six are run by the same national organisation. Ten of the sites are hospices, providing end-of-life care to their populations, one site provides a service jointly organised between local hospices and a NHS Trust, and one site is a charity providing care and services to people with substance abuse issues.

### Eligibility for sites to join the study

Sites that will participate in this study have been selected as part of a government funded initiative to support social action at the end-of-life in England. A number of organisations tendered to provide these services against a set specification, and were then shortlisted for interview. Selection considerations at shortlisting and interview included the sites’ match to the tender, their capacity to deliver the proposed service, and their ability and willingness to contribute to the evaluation of these services. All sites were aware at interview that they would be providing their services in the context of this study design (Wait-list trial and case study evaluation).

## Study population

### Inclusion and exclusion criteria

#### Patient participant inclusion and exclusion criteria

Outside a trial context, it is anticipated that a wide variety of people could be referred to such services with a range of prognosis, diagnosis and backgrounds. We therefore propose the widest possible inclusion criteria to ensure that as many people as possible are eligible (to match likely future service referral criteria).

##### Inclusion criteria

Those eligible to be referred to an end of life care service determined by the referring organisation/individual. They should be able to answer ‘no’ to the ‘surprise question’: ‘Would you be surprised if the patient dies within a year?’Able to give informed consent.

##### Exclusion criteria

Age <18 yearsThose who only understand or speak a language in which our main outcome measure (the WHOQOL-BREF) is unavailable. This is anticipated to be a very small number of potential participants as the WHOQOL-BREF is available in a wide range of languages, including the main languages spoken in the participating sites.Those with an anticipated prognosis of < 4 weeks

#### Family/informal carer

At inclusion, patient participants will be asked to also identify a family member/informal carer to participate in the study. Carers, who may or may not be family members, will be defined as lay people in a close supportive role who share in the illness experience of the patient [20] or provide emotional support. Patients who are unable to identify a family member or informal carer at inclusion will not be excluded from the study.

### Qualitative case study eligibility criteria

The patient participant inclusion criteria for those invited to participate in the qualitative component of the study are the same as for the trial component. Family members/informal carer and those involved in managing and providing the intervention (e.g. volunteers, service managers, health and social care professionals etc.) will be also invited to participate in interviews.

Informal/family carer inclusion criteria for qualitative case study interviews:Identified as a family/informal carer by the patient participating in the trial/qualitative case studyOver 18 yearsAble to give informed consent at the time of the interview

Volunteer/staff inclusion criteria for qualitative case study interviews:Involved in provision or management of the service providing the social action befriending service at the chosen case study site.

### Study sample size

#### Trial study size

Sites funded to provide these services provided an estimate of likely referral numbers to their services. These aggregated numbers indicate that 700 participants are likely to be referred to the service in the specified trial time period which indicates a maximum potential study size of 350 patients in the intervention arm and 350 patients in the wait-list arm of the study recruited from the 12 sites across England involved in the study. Given that each eligible patient will be asked to nominate a carer, the total number of carers to be recruited will be up to 700.

#### Qualitative study size

Three to six (patients, informal carers and volunteers) and two to three (key managers or co-ordinators) will be invited to an interview per case study site. Eight sites will be selected according to their geography and provider type from the 12 sites involved in the study comprising a total sample size of 88–168 participants.

### Power calculation and sample size

#### Trial power calculation and sample size

Three hundred fifty patients per arm are considered to be sufficient to examine the impact of social action services (intervention) on quality of life (primary outcome). Trial power was estimated using a worst case scenario assuming 5 % attrition at primary outcome measure. With 350 or more participants per arm power will exceed .80 to detect difference in change over time corresponding to an effect size of f = .10 (considered a small effect size) between the intervention and wait-list groups. This power model uses alpha = .05, two tailed, and uses a conservative correlation of *r* = .6 for scores lagged 4 weeks, and *r* = .5 for 12 weeks.

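### Power above .80 is presented as a worst case, but it rests on the maximum possible recruitment and on 5% attrition that the protocol does not support as a worst case

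*Protocol article*

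**What the plan says.** Three places in the protocol article bear on the power statement.

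- *Trial power calculation and sample size*: "Trial power was estimated using a worst case scenario assuming 5 % attrition at primary outcome measure". The claim that rests on this is: "With 350 or more participants per arm power will exceed .80 to detect difference in change over time". The target is given as f = .10 and described as small. The test is two-sided at .05, with a correlation of .6 at a 4-week lag and .5 at 12 weeks.
- *Trial study size*: sites' estimates add up to 700 likely referrals, which is said to give a "maximum potential study size of 350 patients in the intervention arm" and the same number in the wait-list arm.
- *Wait-list randomised controlled trial*: the short wait is justified partly because life expectancy is short, with "attrition due to illness or death highly anticipated".

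*Trial recruitment and informed consent procedure* places eligibility assessment and written consent between referral and randomisation. *Participant timeline* says that people who withdraw from the service need not complete questionnaires. The article gives no consent rate, and no attrition rate other than 5%.

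**The concern.** The number that is an upper limit in one section is used as a lower limit in the next. Nothing is deducted for ineligible referrals or refusals, although both are built into the procedures. The attrition allowance is called a worst case, yet the design section gives expected loss as a reason for keeping the wait short. Participants are people whose death within a year would not surprise the referrer, and follow-up is by posted questionnaire.

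This paragraph is the article's only justification of the trial's size. A reader told that power exceeds .80 in the worst case would take a null result as good evidence against a small effect. If recruitment or return of questionnaires falls short of these assumptions, that inference may not be justified.

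**Working it through.** **Inputs from the article.** Two-sided alpha .05; f = .10; r = .6 between baseline and week 4; 350 per arm; 5% attrition, so 350 × 0.95 = 332.5 per arm analysed. For two equal groups f = .10 corresponds to d = 2f = 0.20 outcome SDs. This translation is an assumption, because the article does not say on what scale f is defined.

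**Reproducing the stated power (change score).**
- SD of change = √(2(1 − r)) = √0.8 = 0.894.
- Standard error = 0.894 × √(2/332.5) = 0.0694.
- Ratio = 0.20/0.0694 = 2.88.
- Power ≈ Φ(2.88 − 1.96) = .822, which satisfies the stated inequality.

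**Number needed for .80.** n per arm = 2(1.96 + 0.8416)² × variance/0.20².
- Change score: 2 × 7.849 × 0.8/0.04 = 314. Tolerable combined loss from 350 is 1 − 314/350 = 10.3%.
- Baseline-adjusted, residual variance 1 − r² = 0.64: 2 × 7.849 × 0.64/0.04 = 251.2, so 252. Tolerable combined loss is 1 − 252/350 = 28%. Power at 332.5 per arm is .897.

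The second model is closer to the one in *Comparison between arms*, a mixed model that assumes a common initial mean.

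**Power as uptake and loss vary.** Analysed per arm = 350 × uptake × (1 − loss). The rates are assumptions. Each cell gives change score / baseline-adjusted.

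| Referrals randomised | 5% loss | 10% loss | 20% loss | 30% loss |
|---|---|---|---|---|
| 100% | .822 / .897 | .801 / .881 | .754 / .841 | .697 / .790 |
| 90% | .781 / .864 | .759 / .845 | .709 / .801 | .651 / .747 |
| 80% | .732 / .822 | .709 / .801 | .658 / .754 | .600 / .697 |
| 70% | .674 / .769 | .651 / .747 | .600 / .697 | .544 / .639 |

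**A third scale for f.** In the default repeated-measures formula for a group-by-time interaction with two visits, the noncentrality is f² × N × 2/(1 − r). With N = 665 this is 0.01 × 665 × 2/0.4 = 33.25. Power then exceeds .99, and about 159 participants in total suffice for .80. On that scale f = .10 means a between-arm difference in change of 0.40 SD.

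**The case against.** The strongest reply is that the stated power is correct under its stated inputs, and that is so. A reader might infer an arithmetic error; there is none. Four further inferences also go beyond the documents.

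- *That the power holds only if every referral is randomised.* The limit is on combined loss. With 95% randomised and 5% attrition, 350 × 0.95 × 0.95 = 315.9 per arm remain, just above the 314 needed for a change score. Baseline adjustment allows much more.
- *That the figure fits only d = 0.20 on a change score.* The article states an inequality and names no model. Baseline adjustment and the interaction scale satisfy it too. A 0.40 SD difference is hard to square with the description of the effect as small, but this does not show which scale was used.
- *That r = .5 reduces power to .73.* That value comes from a change score with r = .5 and 332.5 per arm. The .5 belongs to the 12-week lag, and week 12 is collected in the wait-list arm only, after that arm has started the service. No two-arm contrast corresponds to it.
- *That the article forecasts a high attrition rate.* It says that attrition is strongly expected and gives no rate, so the size of any shortfall is unknown.

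It is also fair that the article openly calls 350 per arm a maximum, and that a condensed article may leave the formula and a power table to the full protocol. Their absence alone would not be a finding. What remains is what the article does state: a ceiling used as a floor, and a worst-case label that conflicts with its own account of expected loss.

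**Conclusion.** The point holds as a mislabelled assumption and an internal contradiction. Power above .80 is a best-case recruitment figure with light loss, and no section supports calling it a worst case. This part needs no power model, since it follows from comparing the sections.

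The size does depend on the model. With d = 0.20 and r = .6, power falls below .80 when non-randomisation and attrition together exceed about 10% (change score) or about 28% (baseline-adjusted). At an assumed 20% loss it is .75 or .84 with all 700 randomised, .66 or .75 with 80% randomised, and .60 or .70 with 70% randomised. If f was defined on the default interaction scale, power stays well above .80 throughout these scenarios, but for an effect twice as large in SD units. The article does not allow a choice between these readings, so no single corrected power can be given.

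**What to change.** Rewrite the power paragraph as follows.

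1. Remove the words *worst case* and *or more*.
2. Describe 350 per arm as the recruitment ceiling, reached only if all 700 expected referrals are randomised.
3. Name the power model and the scale of f = .10, preferably as a standardised between-arm difference at week 4, the last assessment before the wait-list arm starts the service.
4. Restate power for the week-4 contrast over a small range of uptake and week-4 loss, for example 70% to 100% of referrals randomised and 5% to 30% lost, marked as assumptions.

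The cost is one paragraph. The stated power becomes conditional and less favourable. No additional patients and no design change are needed.

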#### Case study sample size

A sample size of 8 organisational case studies is considered to be sufficient to understand the processes and determinants that can potentially maximize or minimise the impact of social action services (intervention) on end of life experience. Cases will be sampled from individual study sites chosen on the basis of their geography in order to i) maintain a balance between the South and North of England and ii) maximise heterogeneity on the basis of the type of the service provider (e.g. hospice, social care or voluntary sector organisation).

### Study procedures

The risk of sites experiencing challenges with study procedures will be minimised by providing study sites with clear information with what the study involves, providing access to members of the research team, to answer queries and address problems experienced by each study site. Participants’ engagement with the intervention will be facilitated via a detailed participant information sheet explaining the nature and the particulars of the study that will be handed out to all participants prior to commencing the study.

#### Trial recruitment and informed consent procedure

All those referred to the participating services will be invited to take part in the study. Services will be provided with information to give to potential referrers so that they understand the trial component of service delivery, and the trial eligibility criteria. Appropriately trained staff at the sites receiving referrals (with Good Clinical Practice and study specific training on trial and consent procedures) will assess all referrals for eligibility for the study against trial criteria. Those who are eligible will be given an invitation letter and participant information sheet and given time to ask questions and consider trial participation. Once a referred patient has indicated that they are happy to participate in the trial, the informed consent documentation will be explained to them and written consent taken. These staff are also responsible for informing Lancaster University of ay adverse events. Baseline data will then be collected. At this point the site will contact Lancaster University as part of the randomisation procedure, and plan intervention delivery according to the assigned trial arm.

For trial participants who are receiving their service within a chosen case study site, a proportion of them may be invited to participate in a qualitative interview to discuss their experience of the service. Participants will give consent for this at initial recruitment and again give written consent prior to interview.

